### Statistical analyses

The primary feasibility outcome is defined as the number of participants randomised out of the people considered eligible for being randomised in the trial. Based on observations regarding pretreatment attrition in CBT and IBT for anxiety disorders studies [9, 36–38], we will consider the feasibility outcome satisfactory if it is over 50 %. Our hypothesis is that we are sampling from a population of eligible people of whom at least half will be randomised. If we let *N* be the observed number of eligible people needed to randomise a sample of 64 participants, then in a random sample of size *n* sampled from a population sized *N*, *n/N* follows a binomial distribution with a lower 95 % CI of over 50 % [39, 40]. The sample size estimated from the primary feasibility outcome implicitly defines the sample sizes to be used in the assessment of the exploratory clinical outcomes (Table 1).

The secondary feasibility outcome for the participants in the experimental group is defined as the number of participants completing at least six out of nine FearFighter™ sessions. This feasibility outcome is considered satisfactory when the lower 95 % CI is over 60 % based on observations for completer fractions in IBT for anxiety disorders [9, 41]. In a random sample of size *n* of completers sampled from a population sized *N* of participants in the experimental group, *n*/*N* follows a binomial distribution with a lower 95 % CI over 60 %.

The exploratory clinical outcomes will be analysed using the general linear model (GLM) logistic regression, or the proportional odds model for ordinal outcomes as appropriate, adjusting for the stratification variables and baseline scores of the outcomes according to Table 2. We will calculate two-sided tests and use the resulting *p* values as a data-reducing device because test results with *p* values < 0.05 will be used to select hypothesis-generating outcomes.

**Table 2 Tab2:** Feasibility outcomes and exploratory clinical outcomes in the Fearfighter™ feasibility trial

	Rating scales	Type of outcome	Test
Feasibility outcome			
Number of randomised participants/eligible persons	Not relevant	Proportion	Calculate the probability that 64/*N* can have been obtained in a random sample of *N* participants obtained from a population of persons where half the eligible persons can be randomised. (*N* is the observed number of eligible persons necessary to examine to randomise 64 participants)
Number of participants complying at least 6/9 FearFighter™ sessions/ randomised participants	Not relevant	Proportion	Test analogous to the above feasibility outcome with the difference that now we want to secure that the sample is not from a population being less than 60 % compliant
Exploratory outcome			
Number of participants who no longer fulfil the diagnostic criteria for an anxiety disorder	MINI	Proportion	Fisher’s exact test and logistic regression adjusted by the protocol-specified stratification variable (the result of the latter test is the primary of the 2 tests)
Severity of anxiety	BAI	Continuous	The general linear univariate model (GLM) taking stratification variables and baseline BAI into account
Psychological distress and psychopathology	SCL-90-R	Continuous	GLM taking stratification variables and baseline SCL-90-R into account
Positive well-being	WHO-5	Ordinal	The proportional odds model for ordinal response taking stratification variables and baseline WHO-5 into account (if conditions are not fulfilled, then nonparametric Mann-Whitney)
Functional impairment	SDS	Continuous	GLM taking stratification variables and baseline SDS into account.
Number of randomised receiving psychological treatment during the 9 weeks	Interview	Proportion	Fisher’s exact test and logistic regression adjusted by the protocol-specified stratification variable (the result of the latter test is the primary of the 2 tests).
Number of participants with one or more adverse event	Interview	Proportion	Fisher’s exact test and logistic regression adjusted by the protocol-specified stratification variable (the result of the latter test is the primary of the 2 tests)

*BAI* Beck Anxiety Inventory, *MINI* Mini International Neuropsychiatric Interview*, SCL-90-R* Symptom Checklist-90 revised, *SDS* Sheehan Disability Scale, *WHO* World Health Organisation

We have added one additional exploratory outcome, namely the proportion of participants in the experimental and control groups who are compliant with the randomised intervention, defined as the absence of any psychological treatment during the 9-week intervention period. This outcome, as well as the proportion of participants experiencing an adverse event, will be analysed as the other exploratory outcomes with Fisher’s exact test and logistic regression, adjusted by the protocol-specified stratification variable (the result of the latter test is the primary of the two tests). Adverse events will also be reported according to type, severity, and probable relation to the interventions for the two intervention groups.

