**Methods and design:**

We will conduct an investigator-initiated, feasibility randomised controlled trial. Sixty-four participants are expected to be recruited via an advertisement posted on the homepage of the Student Counselling Service in Denmark. The inclusion criterion for participation in the trial will be the presence of anxiety disorder as assessed with the Mini International Neuropsychiatric Interview. The exclusion criteria will be suicidal risk, an ongoing episode of bipolar disorder or psychosis, concurrent psychological treatment for the anxiety disorder, considered unable to attend the intervention as planned (due to vacation, work/study placement, sickness, or similar occurrences), or lack of informed consent. The intervention group will be offered nine sessions with the ICBT programme FearFighter™ and a weekly telephone contact to support compliance. The control group will receive no intervention. We define the feasibility outcomes as follows: the fraction of randomised participants out of the eligible people (the lower 95 % confidence interval (CI) ≥ 50 %); and the fraction of compliant participants (those receiving at least six out of nine sessions) in the intervention group (the lower 95 % CI ≥ 60 %). The exploratory clinical outcomes are the number of participants no longer meeting the diagnostic criteria for an anxiety disorder at the end of the trial and level of distress (Beck Anxiety Inventory, Symptom Checklist-90-R, WHO Well-Being Index, Sheehan Disability Scale); the number of severe adverse events; and the occurrence of any psychological treatment outside the trial.

To prevent bias in design, and in the gathering and analysis of data throughout the trial, we will follow the SPIRIT 2013 statement which defines standard protocol items for clinical trials.

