## Methods/design

### Trial design

The trial is an investigator-initiated, feasibility randomised controlled trial investigating ICBT with FearFighter™ compared with no intervention for adults with an anxiety disorder. We have followed the Standardised Protocol Interventions: Recommendations for Interventional Trials (SPIRIT) 2013 Statement which defines standard protocol items for clinical trials [20]. The Copenhagen Trial Unit (CTU) is responsible for the centralised randomisation. The randomisation is carried out according to a web-based computer-generated allocation sequence with varying block sizes kept unknown to the investigators. Once a participant is assessed as eligible for the trial the trial secretary will use the web-based randomisation system to allocate the participant to an intervention group. The allocation ratio is 1:1. Based on evidence of prognostic factors, the randomisation is stratified into: (1) social phobia and panic with agoraphobia, and (2) panic disorder without agoraphobia and specific phobia [21, 22]. Participants with panic disorder without agoraphobia and specific phobia have a distinctively higher remission rates than other types of anxiety [21, 22]. Assessment will be conducted prior to randomisation and start of intervention (week 0), at post-intervention (week 10), and at follow-up (week 37) (see the flow chart in Figure 1 in the Appendix). The trial has been approved by the Regional Ethical Committee for the Capital Region of Denmark (journal number: H-15005836), and by the Danish Data Protection Agency (journal number; RHP-2015-009 I-Suite 03652). The trial is registered at ClinicalTrials.gov at the United States National Institutes of Health (Identifier: NCT02499055, registered on 1 July 2015).

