### Exploratory clinical outcomes

The primary exploratory clinical outcome is the proportion of participants who no longer fulfil the diagnostic criteria for an anxiety disorder at the end of the intervention as assessed with the MINI [26]. Other exploratory clinical outcomes are severity of psychiatric symptoms, disability, and well-being measured using the following described participant-reported instruments: the Beck Anxiety Inventory (BAI) is a 21-item general questionnaire for anxiety symptoms during the last 14 days rated on a 4-point Likert scale from 0 to 3. The maximum score is 63. A score of 26 or greater indicates severe anxiety [31]. The Symptom Checklist-90 revised (SCL-90-R) is a 90-item multidimensional questionnaire measuring psychopathology and psychological distress during the last 7 days on nine primary symptom dimensions and three global dimensions. Each item is rated on a 5-point Likert scale from 0 to 4. The score on each dimension is the mean of the included items [32]. The Global Severity Index (GSI), interpersonal sensitivity dimension (IS), anxiety dimension (ANX), and phobic anxiety dimension (PHOB) are used in this trial. The SCL-90-R is a valid and reliable outcome, used often in psychotherapy research, and Danish norms are available [33]. The Sheehan Disability Scale (SDS) is a 3-item questionnaire for occupational function, social function, and family function rated on an 11-point Likert scale. Specific scoring for the three functions is from 0 to 10 and a global score for the general function is from 0 to 30. A score of 5 or greater on the specific scales indicates dysfunction [34]. The WHO Well-Being Index is a 5-item questionnaire for the assessment of health-related quality of life for the last 14 days on a 6-point Likert scale from 0 to 5. Scores are summated, with raw scores ranging from 0 to 25 [35].

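### The WHO-5 fallback in Table 2, a plain Mann-Whitney test, drops baseline WHO-5 and the stratum, so precision is lost if it is used (minor; exploratory outcome)

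*Protocol article*

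**What the plan says.** The Statistical analyses section says the exploratory clinical outcomes will be modelled "adjusting for the stratification variables and baseline scores of the outcomes according to Table 2". In Table 2 the WHO-5 row reads "The proportional odds model for ordinal response taking stratification variables and baseline WHO-5 into account", followed by the exception "if conditions are not fulfilled, then nonparametric Mann-Whitney". No covariate, stratified version or change score is attached to the Mann-Whitney test.

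The other rows of Table 2 work differently:

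- **Score outcomes.** BAI, SCL-90-R and SDS each have an adjusted general linear model and no fallback. The SDS row, for example, is "GLM taking stratification variables and baseline SDS into account".
- **Binary outcomes.** Fisher's exact test stands beside a stratum-adjusted logistic regression, and the logistic result is the primary one.

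Table 1 shows WHO-5 collected at week 0, week 10 and week 37. The Trial design section stratifies randomisation by type of anxiety disorder on prognostic grounds.

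**The concern.** WHO-5 is the only exploratory outcome for which an unadjusted test can take the place of the adjusted analysis. Neither the baseline score nor the stratum would cost anything to use, since both are recorded before treatment starts. A baseline measurement of the same scale usually explains part of the variation at follow-up. Leaving it out widens the uncertainty around the group comparison. Mann-Whitney also gives no adjusted effect estimate to set beside those for BAI, SCL-90-R and SDS.

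The stake is limited but real. The article uses p values below 0.05 to pick which exploratory outcomes are carried forward as hypotheses. With a less precise test, a true well-being signal is more likely to be left behind.

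**Working it through.** The article states no power or precision figure for WHO-5, so there is none to reproduce. The sample size rests on the feasibility proportion.

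**Inputs from the article.** "Sixty-four participants are expected to be recruited" and "The allocation ratio is 1:1" give 32 per arm. Tests are two-sided, with 0.05 as the selection threshold. WHO-5 has 26 possible values: "Scores are summated, with raw scores ranging from 0 to 25".

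**Assumed inputs.** The baseline-outcome correlation r is taken as 0.3, 0.5 and 0.7. The SMD is taken as 0.5, with 0.3 and 0.79 as a range. The Background cites 0.79, but for self-rated anxiety against waitlist and not for WHO-5.

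**Step 1: formula.** With n per arm and residual SD s in units of the outcome SD, power ≈ Φ(SMD × √(n/2) / s − 1.96).

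- Adjusted for baseline: s = √(1 − r²), n = 32.
- Mann-Whitney: s = 1 and n = 32 × 0.955 = 30.56, where 0.955 is its asymptotic efficiency relative to the t test for normal data.

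**Step 2: SMD 0.5.** Here √(32/2) = 4, so the numerator is 0.5 × 4 = 2.00.

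- Mann-Whitney: 0.5 × √15.28 = 1.95; Φ(1.95 − 1.96) ≈ 50%.
- r = 0.3: 2.00/0.954 = 2.10; Φ(0.14) ≈ 55%.
- r = 0.5: 2.00/0.866 = 2.31; Φ(0.35) ≈ 64%.
- r = 0.7: 2.00/0.714 = 2.80; Φ(0.84) ≈ 80%.
- r = 0: 2.00/1 = 2.00; Φ(0.04) ≈ 52%, so about 2 points are lost.

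**Step 3: range of SMD.**

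| SMD | Mann-Whitney | Adjusted, r = 0.3 | r = 0.5 | r = 0.7 |
|---|---|---|---|---|
| 0.3 | 22% | 24% | 28% | 39% |
| 0.5 | 50% | 55% | 64% | 80% |
| 0.79 | 87% | 91% | 95% | 99% |

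**Step 4: check by simulation.** Scores were rounded and clipped to 0–25 (assumed mean 10, SD 4.5), with 1,500 trials per setting. The adjusted proportional odds model was compared with Mann-Whitney:

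- r = 0.5, SMD 0.5: 64% against 49%.
- r = 0.5, SMD 0.79: 95% against 87%.
- r = 0.7, SMD 0.5: 76% against 48%.

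In smaller runs of 400 trials with no treatment effect, Mann-Whitney rejected in about 4% to 6%, so its type I error is kept. The stratum was given no effect on the score, so these losses come from the baseline score alone.

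**Step 5: in sample-size terms, once the fallback is used.** An unadjusted comparison of 64 people is worth an adjusted one of 64 × (1 − r²): 58, 48 and 33 people at r = 0.3, 0.5 and 0.7. This is before the small extra loss from using ranks.

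**The case against.** The strongest reply is that the planned WHO-5 analysis is already adjusted, and that Mann-Whitney applies only if something goes wrong. That stands. The figures above describe a trial that has switched, not the plan on average. A reader might infer that the plan gives up 25% to 49% of its sample. That range is r² at r = 0.5 and 0.7 (0.25 and 0.49), and it holds only after the switch and only at those assumed correlations.

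How often the switch happens is open. If the conditions mean a global score test of proportional odds, simulation at n = 64 had it reject in 4% of trials under true proportional odds and in 12% when the treated arm's SD was doubled. Multiplying by the 15-point gap at r = 0.5 and SMD 0.5 gives an average loss of roughly 0.04 × 15 = 0.6 to 0.12 × 15 = 1.8 points. This treats the gap as the same in trials that switch. The article does not name the check, so another criterion could give another rate.

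Three further readings are tempting, and the article does not support them:

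- **A contradiction with the Statistical analyses section.** That section adjusts as laid out in Table 2, and Table 2 contains the exception. The fallback departs from the pattern of the other rows without breaking the rule.
- **An unreliable trigger.** With 26 possible values and 64 people, a proportional odds check would have little power. But that reading of the conditions is an inference, and the criterion may sit in an analysis plan that is not shown.
- **A wrong primary model.** Treating a 0–25 sum as ordinal while treating the 0–30 SDS sum as continuous is a modelling choice, and either is defensible.

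It also stands that the fallback is stated in advance, that the analysis is done with coded groups, and that feasibility is judged on randomisation and completion alone.

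**Conclusion.** The point holds for the fallback only. As written, it discards baseline WHO-5 and the stratum, which the planned model and every other score outcome use. If it is applied with 32 per arm and an assumed SMD of 0.5, the power given up is about 6, 14 and 30 points at assumed correlations of 0.3, 0.5 and 0.7, and about 2 points at zero. Across SMDs of 0.3 to 0.79, the loss is about 3 to 6, 7 to 14 and 12 to 30 points at those three correlations.

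This is a loss of precision and of consistency between outcomes. It is not bias, and the false-positive rate is not inflated. No overall loss for the plan can be fixed from the article, because the trigger rate is unknown. Severity is minor: WHO-5 is one exploratory outcome in a feasibility trial.

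**What to change.** In the WHO-5 cell of Table 2, replace Mann-Whitney with a fallback that keeps both covariates. Two options fit the plan:

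- rank ANCOVA of the week 10 or week 37 WHO-5 score on baseline WHO-5 and stratum; or
- the baseline- and stratum-adjusted general linear model already specified for SDS.

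Mann-Whitney can stay as a sensitivity analysis beside the adjusted result, in the way Fisher's test stands beside the logistic model for the binary outcomes. The proportional odds model can remain the main analysis.

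The cost is one table cell and no new data, since the baseline score and the stratum are already recorded. The change should be made before the group codes are broken.

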### Support person and support manual

Each trial participant is contacted over the telephone by a support person once a week during the 9 weeks of intervention. Each telephone contact should take about 10 min and a maximum of 1.5 h for the whole intervention period. The purpose of the contact is to secure and assess compliance and also to assist the participant’s adherence to the programme. The support person follows a support manual for the amount, type, and content of the support given. The support person must not engage in a psychotherapeutic dialogue with the participants. The support person who performs all the initial interviews and baseline assessments will also support the 32 participants in the experimental group. The reason for this is to optimise the alliance between the participants and the support person.

The manual for the support person prepared by the company behind the Danish version of FearFighter™ was tested by us, the trial investigators, and found to be too unspecific and vague for having standardised support in our trial. Therefore, we prepared our own manual with specific instructions for the support at each session in FearFighter™. None of the instructions in our manual are in conflict with, or violate the general instructions in, the support manual by the Danish company. Both the original support manual and our manual are written in Danish and can be obtained upon request.

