Serious adverse events and other untoward events that require hospitalisation, are life-threatening, or result in death are collected following the SPIRIT recommendations [20]. All adverse and untoward events will be categorised and summated. Finally, the proportion in the groups of experimental and control participants who are compliant with the randomised intervention, defined as the lack of any psychological treatment during the 9-week intervention period, will be registered. At follow-up, it will be registered if participants have been engaged in psychological treatment since the end of the trial, although no restrictions will be imposed on the participants during the follow-up period.

All scores will be compared between the two groups at post-treatment (week 10) and at follow-up (week 37). Serious adverse events and other untoward events will be gathered during the intervention for the intervention group and at post-treatment for both the control and the intervention groups.

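### For adverse events and outside treatment, the primary test is ordinary logistic regression with no sparse-data rule, so it gives no odds ratio if one arm of 32 has no events

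*Protocol article*

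**What the plan says.** The Statistical analyses section of the protocol article and its Table 2 name two tests for each binary clinical outcome: Fisher's exact test and a logistic regression adjusted for the stratification variable. The section ranks them for outside psychological treatment and adverse events: "adjusted by the protocol-specified stratification variable (the result of the latter test is the primary of the two tests"). Table 2 repeats the ranking in each binary row: "the result of the latter test is the primary of the 2 tests". No penalised or exact form of the regression is named, and nothing covers an empty cell. The WHO-5 row of the same table does have a fallback, the Mann-Whitney test, if the model's conditions fail.

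On testing, the section says "We will calculate two-sided tests" and that p "values < 0.05 will be used to select hypothesis-generating outcomes". It does not say whether the logistic p value is a Wald or a likelihood-ratio one.

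On size, the abstract says "Sixty-four participants are expected to be recruited", Trial design says "The allocation ratio is 1:1", and the support person "will also support the 32 participants in the experimental group".

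On the events themselves, Exploratory clinical outcomes describes serious and other untoward events "that require hospitalisation, are life-threatening, or result in death are collected".

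**The concern.** Maximum-likelihood logistic regression needs events and non-events in both arms to estimate a treatment effect. With 32 per arm, an uncommon outcome can easily leave one arm without events, and the analysis ranked first then cannot produce its estimate.

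The ranking is fixed in the text, so this is a stated rule that fails for some data, not a detail left for later. At stake are the comparison of harms and of co-treatment between arms, and how the p<0.05 screen treats these two outcomes. If the team turned to another test after seeing the model fail, that choice would be data-driven.

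**Working it through.** **Inputs.** 64 randomised 1:1 (abstract; Trial design), two-sided testing at 0.05 (Statistical analyses), and a model with arm and stratum. The documents give no event rates, so every rate below is an assumption. The model fits assume a binary stratum split evenly, 16 per arm and stratum, with events spread as evenly as possible over the strata.

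**1. Arm size.** 64 / 2 = 32, which matches the 32 in the section on the support person.

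**2. Why the estimate is missing.** A participant without an event contributes −log(1 + exp(η)) to the log-likelihood, where η is the linear predictor. If an arm has no events, its whole contribution keeps rising as its η falls, so the likelihood has no maximum at a finite treatment coefficient. Software stops at an arbitrary large value with a huge standard error.

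**3. What each method returns for 0/32 v k/32.**

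| k | Wald p | Likelihood-ratio p | Fisher p | Firth p |
|---|---|---|---|---|
| 3 | 0.999 | 0.038 | 0.238 | 0.10 |
| 4 | 0.999 | 0.016 | 0.113 | 0.049 |
| 5 | 0.999 | 0.007 | 0.053 | 0.022 |
| 6 | 0.999 | 0.003 | 0.024 | 0.010 |
| 8 | 0.999 | 0.0005 | 0.005 | 0.002 |

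At k = 6 the fitted log odds ratio is about 22 in absolute value, with a standard error of about 14,000. Firth's estimate at k = 6 is finite: 0.065 for the empty arm, or 1/0.065 ≈ 15 the other way round.

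**4. Chance of at least one empty arm.** At a common rate p this is 1 − (1 − (1 − p)^32)^2.
- p = 2%: 0.98^32 = 0.524, so 1 − 0.476^2 = 77%
- p = 5%: 0.95^32 = 0.194, so 1 − 0.806^2 = 35%
- p = 10%: 0.90^32 = 0.034, so 1 − 0.966^2 = 7%
- p = 15%: 0.85^32 = 0.0055, so 1 − 0.9945^2 = 1%

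The 77% includes 0.524^2 = 27% with no events in either arm, where no test is informative.

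**5. Chance that a Fisher-significant difference comes with no finite odds ratio.** Against an empty arm, Fisher's test first reaches p<0.05 at 6 events (5 gives 0.053). With X1 and X2 the event counts in the two arms, the chance is (1 − p1)^32 × P(X2 ≥ 6) + (1 − p2)^32 × P(X1 ≥ 6).
- Equal rates: under 0.01% at 2%, 0.2% at 5%, 0.6% to 0.7% at 10%
- 2% v 10%: 5%
- 5% v 20%: 12%
- 2% v 20%: 0.524 × 0.640 = 34%, the second term being negligible

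**6. Size of the alternatives.** By exact enumeration without the stratum, at a nominal 5%, Fisher's true size is about 0% at a 2% rate, 0.2% at 5% and 1.1% at 10%. The likelihood-ratio test's size is 2.7% at 2%, 5.3% at 3%, 8.6% at 5%, 7.2% at 10% and 5.5% at 15%.

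**The case against.** **Rarity is not stated.** The clause on hospitalisation, threat to life and death points to rare events. However, Table 2 counts participants with any adverse event, and the protocol also says that all such events will be categorised. For outside treatment, controls receive nothing, recruitment runs through a counselling service, and everyone is told where else help is available. At 15% per arm an empty arm has only a 1% chance. This stands, and it is why the result is given as a range.

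**A reader might infer that the screen will discard a harm signal.** The documents do not support that. It follows only if a Wald test is used, which the protocol does not say; a likelihood-ratio test would keep 0 v 6. Fisher's result would still be reported, as would adverse events by kind, grade and likely link to the intervention, so a 0 v 6 split would be visible.

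**A reader might take 77% or 35% as the chance of losing a signal.** Those figures count any empty arm at equal rates. The chance of a Fisher-significant result without an estimate is under 1% there, and becomes material only when the rates differ widely.

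**A reader might call the likelihood-ratio test badly liberal, or Fisher's test the obvious primary.** Neither is well supported. The likelihood-ratio inflation is moderate and confined to a middle band of rates. Fisher's test is strongly conservative here and drops the stratum: at 2% v 10% it rejects in 5% of trials, against 37% for the likelihood-ratio test.

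**Details may be left to an analysis plan.** The test statistic may be. The ranking is not, because the protocol states it, and it has no fallback where the WHO-5 row has one.

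**Conclusion.** The point holds in a limited form. The ranking makes primary an analysis that has no finite odds ratio or Wald interval when one arm of 32 has no events. Its p value then runs from 0.003 to 0.999 for the same 0 v 6 data, depending on an unstated choice. That follows from the model and needs no event rate.

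How often it would happen does depend on assumed rates. An empty arm is likely at 2% to 5% per arm and unlikely at 10% or more. The case for rarity is stronger for adverse events than for outside treatment. Loss of a Fisher-significant difference from the primary analysis ranges from under 1% at equal rates to 34% at 2% v 20%.

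Both outcomes are exploratory. The feasibility criteria, on which the trial's success is judged, are untouched. The change is worth making because it is cheap and has to be fixed before the data are seen.

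**What to change.** Keep the stratum-adjusted logistic model as primary for adverse events and outside psychological treatment, but fit it by Firth's penalised likelihood, with a penalised-likelihood p value and a profile interval. For 0 v 6 this gives an odds ratio of about 15 and p = 0.010. Apply the same method to loss of diagnosis on the MINI if a cell is empty. Keep Fisher's exact test as the second analysis. Report event counts per arm with the risk difference and a score interval. If neither arm has an event, report the counts only.

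The cost is one sentence in Statistical analyses and matching entries in the binary rows of Table 2, slight shrinkage of the odds ratio, and a little more analysis work. Sample size and data collection do not change.
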